### Sample Size

The sample size was calculated using the formula for unpaired analytical studies with numerical data. Based on a 95% confidence level (Zα=1.96) and 80% power (Zβ=0.84), the minimum sample size is 16 participants per group, totaling 32 participants.

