**Methods:**

This is a prospective, randomized controlled trial. Patients aged 17‐40 years undergoing odontectomy under general anesthesia at the Dental and Oral Hospital, Universitas Padjadjaran, will be recruited. Participants (n=32) will be randomly assigned to either the intervention group (VR experience of the operating room) or the control group (standard verbal education). Data collection includes salivary samples (alpha-amylase and cortisol), vital signs (blood pressure, heart rate, respiratory rate), and APAIS scores measured at baseline, immediately post-intervention, and 15 minutes post-intervention. Data will be analyzed using independent and paired *t* tests or Mann-Whitney and Wilcoxon tests, depending on normality.

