### Randomization and Blinding

Eligible participants will be randomly allocated (1:1 ratio) into either the Intervention (VR) or Control group. To ensure proper allocation concealment, a computer-generated randomization sequence will be created by an independent researcher not involved in clinical care or data collection. The allocation sequence will be concealed using sequentially numbered, opaque, sealed envelopes, which will only be opened after the patient has consented to participate. Due to the nature of the VR intervention, blinding of patients and the administering clinician is not possible. However, the study will use an assessor-blinded approach; laboratory personnel analyzing the salivary biomarkers, and statisticians conducting the data analysis will be strictly blinded to group assignments.

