## Results

The study is currently in the preparation phase. Data collection is scheduled to take place from May 2026 to July 2026. The analysis will focus on the differences in APAIS scores, sAA levels, cortisol levels, and vital signs between the two groups.

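### The 80% power at 16 per group rests on a difference of about 1 SD in one unnamed outcome; the abstract's t test reaches only 77–80% there, and nobody is enrolled above the minimum

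*Protocol article*

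**What the plan says.** The Sample Size section of the protocol article describes the method in one sentence: "The sample size was calculated using the formula for unpaired analytical studies with numerical data". Its inputs are "Based on a 95% confidence level (Zα=1.96) and 80% power (Zβ=0.84"), and its result is that "the minimum sample size is 16 participants per group, totaling 32 participants". It names no outcome, difference, SD or allowance for loss.

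The abstract plans to enrol exactly that number: "Participants (n=32) will be randomly assigned to either the intervention group". Allocation is 1:1 (Randomization and Blinding).

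No outcome is called primary. The Results section says "The analysis will focus on the differences in APAIS scores, sAA levels, cortisol levels, and vital signs between the two groups". Counting blood pressure as two measures, Outcomes and Data Collection lists seven: APAIS, systolic and diastolic pressure, heart rate, respiratory rate, salivary alpha-amylase and salivary cortisol. Each is taken at three time points.

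Two different analyses are named. The abstract begins "Data will be analyzed using independent and paired" and goes on to *t* tests, with rank tests as the alternative. The Statistical Analysis section instead names a repeated-measures ANOVA with time, group and time-by-group effects, and GEE or Friedman if normality fails.

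**The concern.** A power figure has meaning only for a given outcome, difference and test. Here the 80% has none of these attached, and two z-values alone cannot produce 16; a standardised difference must have been entered. Three questions follow: which difference it was, whether the tests actually named would have 80% power at that difference, and what happens when a sample is lost.

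The answers affect how a non-significant result is read. The comparator is active: ten minutes of verbal education with a flip chart matched to the visual content of the VR video (Intervention section). The contrast is therefore largely the immersive component, and about 1 SD is a large difference to expect from it. If the trial finds nothing, a reader who takes the 80% at face value may conclude that VR adds nothing, when smaller but worthwhile differences had a modest chance of being detected. The Strengths and Limitations section does concede a small sample, but only in relation to generalizability.

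**Working it through.** **Inputs.** From the Sample Size section: two independent means, Zα = 1.96 (two-sided 5%), Zβ = 0.84 (80% power), n = 16 per group. From the abstract: 32 randomised, *t* test. The difference and SD are not given, so 16 cannot be reproduced forwards; it can only be solved backwards.

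**1. Difference implied by the stated figure.** With d = difference/SD,

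n = 2(Zα + Zβ)²/d² = 2 × 2.80²/d² = 15.68/d².

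- n = 16 exactly: d = √(15.68/16) = 0.990.
- n = 15 exactly: d = √(15.68/15) = 1.022.

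Any d from 0.990 up to 1.022 rounds up to 16. In particular d = 1.0 gives 15.68, hence 16. The stated figure is thus consistent with its formula for a difference of about 1 SD.

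**2. Power of the two-sample *t* test.** Exact noncentral *t*, two-sided 5%, df = n₁ + n₂ − 2, noncentrality d/√(1/n₁ + 1/n₂):

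| Analysed per arm | d = 0.99 | d = 1.00 | d = 1.022 |
|---|---|---|---|
| 16 and 16 | 77.3% | 78.1% | 79.9% |
| 15 and 16 | 75.9% | 76.7% | 78.5% |
| 15 and 15 | 74.5% | 75.3% | 77.1% |
| 14 and 14 | 71.3% | 72.1% | 74.0% |

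With 16 per arm, 80% power needs d = 1.024, just above the top of the range in step 1. The *t* test therefore falls short of 80% at every difference consistent with the formula, by between 0.1 and 2.7 percentage points.

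**3. Smaller differences, 16 per arm, same test.** 59% at 0.8 SD, 38% at 0.6 SD, 28% at 0.5 SD.

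**4. Reserve.** Randomised 32 − stated minimum 32 = 0.

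**5. What use of the baseline could change.** The protocol gives no within-person correlation, so these values are assumptions. With baseline adjustment the residual SD is multiplied by √(1 − r²), with 29 df. For 80% power at 16 per arm:

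| Assumed baseline–post correlation | Detectable difference |
|---|---|
| 0.5 | 0.89 SD |
| 0.6 | 0.82 SD |
| 0.7 | 0.73 SD |

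A comparison of changes from baseline behaves differently. Its SD is multiplied by √(2(1 − r)), which equals 1 at r = 0.5 and exceeds 1 below that. A time-by-group test based on change can therefore have more power than the post-only *t* test when r is above 0.5, and less when r is below it.

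**The case against.** Four objections deserve weight.

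- **There is no arithmetic error.** This stands. A 1 SD difference gives 15.68, which rounds up to 16. The article is also condensed, and the difference, SD and any allowance for loss may be in the full protocol. Their absence here would not be a finding by itself.
- **The gap between the normal formula and the *t* test is small.** This stands too. A reader might infer that true power is 77%. That is only the low end; the planning difference is unknown within 0.99–1.022 SD, and the range is 77–80%.
- **Little loss is to be expected.** Measurements are planned for one morning session, with the last 15 minutes after the intervention, so there is no later visit to miss. What remains is failed or insufficient saliva, with 4–5 mL required unstimulated at each of three points. A reader might infer that one lost participant undoes the design. It does not: at the top of the range the protocol's own normal formula still gives about 81% with 15 against 16.
- **The *t*-test figures need not describe the main analysis.** A repeated-measures analysis uses the baseline. At an assumed correlation of 0.7, power at 0.8 SD would be 86% with baseline adjustment or 81% on change scores, rather than 59%; at 0.5 SD it would be 48% or 42%, rather than 28%. So the documents do not establish that moderate effects are mostly undetectable. They do not establish the opposite either, since no correlation is given.

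The protocol also promises effect sizes and 95% confidence intervals, which lessens the risk of misreading a null result. And it nowhere claims 80% power for each of the seven measures, though a reader might infer it from a power figure attached to none.

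**Conclusion.** The point holds as one about how the power is stated and protected, not as an error in the sample size. The stated 80% applies to a difference of 0.99–1.022 SD in one unnamed outcome, under a normal approximation. The *t* test named in the abstract has 77–80% power there and does not quite reach 80% at any difference consistent with the formula. Its power is 59% at 0.8 SD and 28% at 0.5 SD.

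The formula does not describe the repeated-measures ANOVA, whose power could be higher or lower. Enrolment equals the minimum, so any unusable sample takes the trial below it: 74–77% with one lost per arm, 71–74% with two.

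These figures assume a two-sided 5% test, equal SDs, roughly normal data, and that 16 is the formula's own result, as the section presents it. A hidden allowance (14 raised to 16 for 10% loss) is arithmetically possible but is not what the text says.

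**What to change.** Keep N = 32 and change two sections.

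**Sample Size.** Name the one outcome the calculation was made for, then restate along these lines: *16 analysed per arm gives 80% power to detect a difference of 1.02 SD (two-sample t test, two-sided 5%) in that outcome; no power is claimed for the others.* Add power at that difference for 14 and 15 evaluable per arm (about 74% and 77%). If a gain from baseline adjustment is quoted (0.89, 0.82 or 0.73 SD at correlations of 0.5, 0.6 or 0.7), label the correlation as an assumption.

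**Statistical Analysis.** Repeated-measures ANOVA, as usually run in SPSS, drops anyone missing a time point. Replace it with a baseline-adjusted mixed model of the two post-test values, so that a participant missing one post-test sample is kept. Bring the abstract's list of tests into line.

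The cost is a slightly less favourable stated figure and a little more analysis work, with no extra participants. The Results section describes the study as still in preparation, so the change can be made before data are collected.

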### Statistical Analysis

Data will be analyzed using SPSS version 25.0 (IBM Corp). Descriptive statistics will be used to summarize the demographic and clinical characteristics of the participants. The Shapiro-Wilk test will be utilized to assess the normality of the data distribution, given the sample size is less than 50. Because this study involves repeated measurements across three time points, repeated-measures Analysis of Variance (ANOVA) will be conducted for normally distributed data to evaluate the main effects of time, group assignment, and the time-by-group interaction. If the data violate the assumption of normality, non-parametric alternatives such as Generalized Estimating Equations (GEE) or the Friedman test will be applied. To comprehensively report the magnitude of the intervention’s effect, effect sizes (eg, partial eta-squared or Cohen *d*) and 95% confidence intervals will be presented alongside the *P* values. A *P* value of <.05 is considered statistically significant..

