### Outcomes and Data Collection

Data collection occurs at three standardized time points: Baseline (immediately before the VR or verbal education intervention), Post-test 1 (immediately after the intervention), and Post-test 2 (15 minutes after the intervention). The subjective anxiety assessment uses the APAIS, comprising 6 items scored on a 5-point Likert scale, with total scores ranging from 6 to 30, categorized from “Not Anxious” to “Panic.” Objective physiological assessments include blood pressure (systolic/diastolic), heart rate, and respiratory rate, which will be measured after the patient has rested for at least 5‐10 minutes.

For objective biochemical assessments, unstimulated saliva samples (4‐5 mL) will be collected via the spitting method at the three designated time points. To ensure optimal long-term preservation of the stress biomarkers prior to enzyme-linked immunosorbent assay (ELISA) analysis, samples will be initially frozen at −10 °C and subsequently transferred to a −80 °C freezer. Salivary Alpha-Amylase (sAA) will be analyzed to measure sympathetic nervous system activity, while Salivary Cortisol will be measured to assess HPA axis activity.

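### A normality pretest of unfixed form chooses each outcome's analysis after the data are seen; one model per outcome should be named in advance

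*Protocol article*

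**What the plan says.** The Statistical Analysis section of the protocol article sets a two-way switch.

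- The trigger: "The Shapiro-Wilk test will be utilized to assess the normality of the data distribution, given the sample size is less than 50".
- If normality is accepted: "Analysis of Variance (ANOVA) will be conducted for normally distributed data", with time, group and their interaction as effects.
- If it is not: "If the data violate the assumption of normality, non-parametric alternatives such as Generalized Estimating Equations (GEE) or the Friedman test will be applied".

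The Methods paragraph of the abstract has a switch of the same kind but with other tests on both branches: t tests, or "Mann-Whitney and Wilcoxon tests, depending on normality".

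The only significance level given is the general one ("value of <.05 is considered statistically significant"); none is tied to Shapiro-Wilk. Residuals are not mentioned. The design supplies the rest: "Data collection occurs at three standardized time points", and "the minimum sample size is 16 participants per group, totaling 32 participants".

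**The concern.** Three features of the rule are weak.

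1. **It tests the wrong object, on its natural reading.** Repeated-measures ANOVA assumes normal errors given group and time. The rule speaks of the distribution of the data.
2. **It is not one rule.** With two arms and three times, it could mean one, three or six tests per outcome. The route an outcome takes depends on which is chosen, and that choice can be made with the data in hand.
3. **It discriminates poorly at this size.** Normal outcomes are diverted by chance, while a skewed cell of 16 often passes.

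APAIS, blood pressure, heart rate, respiratory rate and two salivary biomarkers all bear on the single hypothesis in Principal Findings. Under the rule, some may be analysed by ANOVA and others by the fallback, with different effect measures, for no reason but chance. Where the fallback is Friedman, a within-subject test with no group term, the outcome loses the time-by-group contrast that answers the trial's question.

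**Working it through.** **The plan's own figure.** The article gives no rate of misrouting, so there is none to reproduce. Its sample size matters here only through the 16 per arm.

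**Inputs from the article.** Two arms (1:1), three time points, 16 per arm.

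**Assumptions, because the article is silent.** Each Shapiro-Wilk test is at 0.05, and any single rejection sends the outcome to the fallback.

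**Step 1. Chance diversion of a truly normal outcome, tests treated as independent.** The rate is 1 − 0.95^k for k tests:

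- k = 1: 5.0%
- k = 2: 1 − 0.95² = 9.8%
- k = 3 (arms pooled, one test per time): 1 − 0.95³ = 14.3%
- k = 6 (each arm at each time): 1 − 0.95⁶ = 26.5%

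**Step 2. Allowing for within-person correlation.** Simulated normal data, 2 × 16 participants, three times, 6,000 runs per row:

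| Correlation | Six cell-wise tests | Three pooled tests | One test, one time point |
|---|---|---|---|
| 0 | 26.1% | 13.9% | 5.1% |
| 0.5 | 26.0% | 14.3% | 5.1% |
| 0.7 | 25.1% | 13.8% | 4.8% |
| 0.8 | 25.1% | 13.3% | 5.3% |
| 0.9 | 21.7% | 11.3% | 4.9% |
| 0.95 | 19.8% | 10.1% | 4.8% |

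So six tests give 20–26%. Three pooled tests give 11–14% for correlations up to 0.9, and 10% at 0.95. One valid test gives 5%.

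**Step 3. All 96 values in a single test.** This is not a valid test, because repeated values from one person are not independent. In simulation it rejects for normal data in about 6%, 12% and 30% of trials at correlations 0.5, 0.7 and 0.9.

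**Step 4. Do the readings agree?** At correlation 0.7, the six-cell, three-pooled and all-values readings disagree about the same truly normal outcome in about 30% of trials.

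**Step 5. Missed skewness.** For log-normal data with log-scale SD 0.3, 0.4 and 0.5 (assumed values), a single cell of 16 is flagged in about 20%, 30% and 41% of simulations. Under the any-of-six reading, the outcome as a whole is flagged far more often, in about 68–93% of trials. Low sensitivity is thus a property of the single cell, not of every reading.

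**Step 6. Raw values or residuals.** Pooling two normal arms of 16 whose means differ by 0.5, 1, 1.5 or 2 SD gave rejection rates of 4.6%, 4.9%, 3.8% and 4.8%. The wrong-object point is sound in principle, but at this size a group shift alone does not drive diversion.

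**Step 7. Type I error.** Normal data, time-by-group test, six-cell gate, correlations 0.5 and 0.8, 6,000 runs each:

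| Procedure | Correlation 0.5 | Correlation 0.8 |
|---|---|---|
| ANOVA alone | 5.1% | 5.0% |
| ANOVA, given a Shapiro-Wilk flag | 4.9% | 5.3% |
| Uncorrected robust GEE alone, no gate | 8.1% | 7.9% |
| Gated ANOVA/GEE | 5.8% | 5.8% |
| Gated ANOVA/multivariate test exact under normality | 5.0% | 4.9% |

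A second set of simulations agreed: 4.4–5.1% for ANOVA given a flag, 7.6–8.1% for GEE alone, 5.6–5.9% gated. The excess comes from uncorrected GEE in a small sample, not from selection by the gate.

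**The case against.** **The form of the test is detail for an analysis plan.** An article may leave cells, level and rejection count to a fuller document, and on that narrow point the objection stands. It does not reach the core: the article states a rule under which the data choose the method, and leaves the destination open as well. More detail would narrow the rule but keep that property.

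**The article never says raw values are tested.** True. That is the natural reading of its wording, not its wording, and Step 6 shows little numerical consequence.

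**The practical harm is limited.** This partly stands. GEE can still test time-by-group, and with equal arms mild skewness in an ANOVA has not been shown to do material harm. The serious case is diversion to Friedman, which the article allows.

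**Stronger readings that a reader might infer, and that the documents do not support:**

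- *One normal outcome in four is misrouted.* This is near the top of the range and needs six cell-wise tests at 0.05 with any rejection counting. The article commits to none of these.
- *Most trials would have at least one outcome diverted.* This compounds that top rate across outcomes and treats them as independent, although systolic and diastolic pressure, for example, are measured together and would be expected to correlate.
- *The gate inflates the 5% error rate.* Step 7 shows no measurable inflation for normal data beyond what small-sample GEE brings by itself.

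The abstract's different tests are a separate inconsistency. They show that the analysis is not settled, but do not make the pretest itself any worse.

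**Conclusion.** The point holds in a limited form. A Shapiro-Wilk pretest of unfixed form selects each outcome's analysis after the data are seen. Under the assumptions stated (0.05 per test, any rejection triggers), chance diversion of a truly normal outcome runs from about 5% with one valid test, through 11–14% with three pooled tests, to 20–26% with six cell-wise tests. A moderately skewed single cell of 16 is flagged about 20–40% of the time. The consequence is inconsistent methods and effect measures across outcomes that serve one hypothesis, and possible loss of the between-arm contrast. No error-rate inflation should be attributed to the gate. This should be changed before data collection, but it does not by itself invalidate the trial.

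**What to change.** - Delete the Shapiro-Wilk decision rule.
- For each outcome, name one model and one scale before data collection, and use it whatever a normality test would show. Original scale suits APAIS and vital signs. A log scale for the biomarkers is a reasonable option, but the documents give no biomarker distribution and do not require it.
- Inspect model residuals as a diagnostic only.
- If a rank or permutation comparison between arms is wanted, name it now as a sensitivity analysis that never replaces the main result.
- Bring the abstract's list of tests into line with the Statistical Analysis section.

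The Results section says the study is still in preparation, so the cost is wording only. Chance rerouting then falls to zero. The price is that mild residual non-normality is tolerated in the main analysis; a sensitivity analysis, if one is named, would be shown beside it.

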### Participants

Participants will be recruited using purposive sampling based on specific eligibility criteria. Inclusion criteria comprise patients aged 17‐40 years who are scheduled for odontectomy of at least two impacted third molars under general anesthesia. Eligible patients must be in good systemic health (American Society of Anesthesiologists, ASA physical status I or II) and have no prior history of surgery involving general anesthesia. To control for confounding factors affecting stress biomarkers, patients will be excluded if they have a history of endocrine disorders, chronic stress conditions, sleep disorders, or are currently taking medications that alter the HPA axis or autonomic response, such as anxiolytics, antidepressants, corticosteroids, or beta-blockers. Patients with visual or hearing impairments that prevent the use of VR will also be excluded. While patients with severe diagnosed psychiatric disorders are excluded to minimize profound psychopathological confounding, patients with general dental anxiety or phobia remain eligible to ensure the clinical generalizability of the findings.

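### Whether an incomplete participant is analysed depends on a normality test: repeated-measures ANOVA and Friedman need all three values of an outcome, GEE does not

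*Protocol article*

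**What the plan says.** All in the Protocol article:

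- Outcomes and Data Collection: "Data collection occurs at three standardized time points" (baseline, directly after the session, and 15 minutes later). The outcomes are APAIS, vital signs, salivary alpha-amylase and salivary cortisol.
- Statistical Analysis, first method: "repeated-measures Analysis of Variance (ANOVA) will be conducted for normally distributed data to evaluate the main effects of time, group assignment", together with the time-by-group interaction. The software is SPSS 25; the procedure is not named.
- Statistical Analysis, switch: "The Shapiro-Wilk test will be utilized to assess the normality of the data distribution". If normality fails, "non-parametric alternatives such as Generalized Estimating Equations (GEE) or the Friedman test will be applied". Nothing says which of the two fallbacks applies when.
- Sample Size: 16 per group, 32 in total, described as the minimum, with no allowance for loss shown.
- Abstract, Methods: "Data will be analyzed using independent and paired" t tests, or Mann-Whitney and Wilcoxon tests. This differs from the Statistical Analysis section, which is the fuller statement and is taken here as the plan.

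**The concern.** The three named methods treat a participant with one missing value differently. Classical repeated-measures ANOVA (SPSS GLM) drops that participant from the outcome altogether, including the values that were observed. Friedman does the same. GEE keeps the observed values. The rule that chooses between them is a test of distributional shape, which has nothing to do with missing data.

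Two things are at stake. The first is precision: with 16 per arm, each deleted participant is about 6% of an arm (1/16). The second is comparability: cortisol, alpha-amylase, APAIS and vital signs could each be analysed on a different set of people, for a reason unrelated to the trial question. If the deleted participants were a selected group in one arm, the randomised comparison for that outcome would no longer be protected.

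**Working it through.** **1. The plan's own figure.** The effect size and SD behind 16 per group are not given, so the figure cannot be reproduced. Solving the usual formula backwards, n = 2·((1.96 + 0.84)/d)², with n = 16 gives d = √(2·2.8²/16) = 0.99 SD. This d is implied, not stated.

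**2. Participants left under complete-case analysis.** Assume each of the three values is missing independently with probability p. The complete fraction is (1 − p)³.

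| p (assumed) | (1 − p)³ | of 32 |
|---|---|---|
| 3% | 0.913 | 29.2 |
| 5% | 0.857 | 27.4 |
| 10% | 0.729 | 23.3 |

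Deletion is per outcome. A failed saliva sample removes someone from that biomarker, not from APAIS or vital signs.

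**3. Cost in power.** For a two-sample comparison at d = 0.99, power = Φ(d·√(n₁n₂/(n₁+n₂)) − 1.96).

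- 16 v 16: 80.0%
- 15 v 16: 78.7%
- 14 v 16: 77.2%
- 13 v 16: 75.5%
- 14 v 14: 74.5%
- 12 v 12: 67.9%

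Each participant lost from one arm costs about 1.5 points. This is for the unpaired comparison used for sample size, not for the ANOVA interaction.

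**4. Direction of bias if loss were selective.** Assume no true effect, 16 per arm, correlation 0.6 between time points, and deletion of the 2 VR participants with the highest stopping tendency. That tendency correlates 0.7 with whatever drives it. The expected top two of 16 standard normal values are 1.766 and 1.285, so the mean of the other 14 is −(1.766 + 1.285)/14 = −0.218. The bias in baseline-to-Post-test-1 change (VR minus control, in SD of a single measurement, negative favouring VR) is −0.218 × 0.7 × the slope of change on the standardised driver.

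- Driver is the rise from baseline to Post-test 1: slope √(2·0.4) = 0.894, bias −0.14.
- Driver is the Post-test 1 level: slope 1 − 0.6 = 0.4, bias −0.06.
- Driver is the baseline level: slope 0.6 − 1 = −0.4, bias +0.06.
- Driver is the average level over the three times: slope 0, bias 0.

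A simulation of 40,000 trials per pattern gave −0.14, −0.06, +0.06 and 0.00. The sign is not fixed.

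**5. Is GEE the safe branch?** This was simulated with the same correlation and no true effect, 600 runs per setting, for baseline-to-Post-test-2 change with 3 of 16 VR participants incomplete (Monte Carlo SE about 0.013).

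| Who is incomplete | Complete-case | GEE, independence | GEE, exchangeable |
|---|---|---|---|
| Highest at Post-test 1; Post-test 2 missing | −0.02 | −0.20 | −0.02 |
| Highest at baseline; both post-tests missing | +0.11 | −0.20 | −0.03 |
| Highest at Post-test 1; both post-tests missing | −0.01 | −0.20 | −0.10 |

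Keeping incomplete participants is not enough by itself. In the first two rows loss depends on observed values, and modelling the within-person correlation brings the bias close to zero. In the third it depends on a value never observed, and the exchangeable model stays biased, here more than the complete cases.

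**The case against.** The strongest reply is that this is missing-data detail, which a condensed article leaves to the full protocol or SAP. That stands for the absence of an analysis set or missing-data rule, and neither is raised here. It does not cover the methods the article does fix. Under normality it commits to repeated-measures ANOVA, so an SAP that retained incomplete participants by another method would have to depart from this text.

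The second reply is that little will be missing. All values come from one session the day before surgery, the last of them 15 minutes after a 10-minute exposure, the VR content was piloted for tolerability, and saliva is required equally in both arms. This is fair, and it limits the point to a safeguard. With complete triplets the choice of method does not change who is analysed.

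Four stronger readings are tempting, and the documents do not support them.

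- A reader might infer that patients who remove the headset are dropped and that this favours VR. No section says a participant who stops is no longer measured, and step 4 shows that even selective deletion can go either way.
- A reader might infer that the GEE fallback retains incomplete participants. Friedman is named alongside it and does not.
- The criterion "Patients with visual or hearing impairments that prevent the use of VR will also be excluded" might suggest exclusions after allocation, in the VR arm only. It is an entry criterion, and Randomization and Blinding allocates only patients already found eligible.
- A single-time t test with 2 VR patients deleted (correlation 0.7) gives 6.4% instead of 2.5% false findings in favour of VR. That calculation ignores baseline and is not the planned analysis. For the time-by-group interaction, a simulation under the step 4 assumptions gave two-sided rejection of 5.2% to 5.4% when stopping tracked average, baseline or Post-test 1 level, and 6.6% when it tracked the rise during the session. The group main effect was more affected in the first three patterns (5.5% to 6.6% one-sided), but it averages in the baseline and is not the natural test of treatment.

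**Conclusion.** The point holds in a limited form. As written, a Shapiro-Wilk result and then an open choice between GEE and Friedman determine, outcome by outcome, whether participants with a missing value are analysed. At assumed missing rates of 3% to 10% per time point, a complete-case method would keep about 29 down to 23 of 32 participants for that outcome. Bias is possible if loss is selective in one arm. In the illustrations it ran from −0.14 to +0.06 SD of baseline-to-Post-test-1 change with 2 of 16 VR participants deleted. The missing rates, the correlations of 0.6 and 0.7 and the loss patterns are all assumptions. The complete-case behaviour is that of classical repeated-measures ANOVA, since the SPSS procedure is not named. Nothing in the documents shows that selective loss will occur or that it would favour VR.

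**What to change.** In Statistical Analysis, replace the repeated-measures ANOVA by a linear mixed model for repeated measures with arm, time and arm-by-time (SPSS MIXED). Fit it to all randomised participants in their allocated arm, using every available time point. If a fallback for non-normal outcomes is kept, name one method that uses the same participants, so that the normality result does not change who is analysed. Bring the Abstract into line.

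In Outcomes and Data Collection, state that participants who end the VR or education session early continue to be measured at both post-tests, and from which moment those times are counted. This does more than any model, because it prevents the missing values.

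The cost is a few sentences and no new software; the Results section describes the study as still in preparation. The model relies on missing-at-random for missed measurements and does not repair loss that depends on unobserved values. Keeping early stoppers in their arm may somewhat dilute the estimated VR effect.

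### The Abstract and the Statistical Analysis section plan different tests, neither uses baseline as a covariate, and no effect is named as the test of VR; one candidate, the three-visit group effect, is diluted.

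*Protocol article*

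**What the plan says.** The article describes the analysis twice.

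- **Abstract, Methods:** "Data will be analyzed using independent and paired" t "tests or Mann-Whitney and Wilcoxon tests, depending on normality".
- **Methods, Statistical Analysis:** a repeated-measures ANOVA "will be conducted for normally distributed data to evaluate the main effects of time, group assignment, and the time-by-group interaction". If normality fails, GEE or the Friedman test replaces it.

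Under Outcomes and Data Collection, every measure is taken at baseline, immediately after the session and 15 minutes later. Baseline is therefore one of the three repeated outcomes. It is not named as a covariate anywhere.

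Participants are "randomly allocated (1:1 ratio) into either the Intervention (VR) or Control group". The Results section says the analysis will focus on differences between the two groups, and the Discussion hypothesizes less anxiety with VR than with verbal education. On size, "The sample size was calculated using the formula for unpaired analytical studies with numerical data" and "the minimum sample size is 16 participants per group, totaling 32 participants", at two-sided 5% and 80% power. No difference or SD is given.

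**The concern.** No test appears in both lists, so the two statements cannot both be the plan. The Statistical Analysis section also lists three ANOVA effects and does not say which one answers the trial's question. The Abstract does not say at which time the independent test is made, or whether it uses raw or change values.

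The candidates are not interchangeable. Some compare the arms efficiently, one compares them on a diluted scale, and several do not compare them at all. If the choice is left open until the data are seen, any of them could be reported as the result. With only 32 patients, the choice can also decide whether a real effect is detected.

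**Working it through.** **1. What each listed test estimates.** Let d1 and d2 be the true arm differences at Post-test 1 and Post-test 2, in SD units. Randomization makes the expected baseline difference 0.

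- *Group main effect:* equivalent to a t test on each patient's three-visit mean. It estimates (0 + d1 + d2)/3, which is 2d/3 if d1 = d2 = d. A simulation at d = 1.0 and correlation 0.6 gave 0.668d.
- *Time-by-group interaction:* tests whether change over time, including change from baseline, differs between arms. The dilution does not apply. It has 2 df, one of which goes to differences between the two post-tests.
- *Independent t / Mann-Whitney:* compare arms, without baseline as a covariate.
- *Time main effect, paired t, Wilcoxon (read as the paired counterpart), Friedman:* change over time, with no comparison of arms. Such change can occur without any VR effect. The Intervention section itself treats salivary cortisol as dependent on time of day.

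**2. The plan's own figure.** Without a difference or SD, 16 per group cannot be recomputed from stated inputs, only back-solved: d = (1.96 + 0.84) × √(2/16) = 0.99. With the same formula, values from 0.99 to 1.02 SD give 16.

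**3. Power at 16 per arm.** Assumptions, none of them stated in the article: d = 0.99 at both post-tests (d² = 0.9801), equal variances, compound symmetry with correlation ρ, two-sided 5%. Noncentral F with n/2 = 8:

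- Group: λ = 8 × (4/9)d² / ((1+2ρ)/3), df 1, 30. ρ = 0.5: 3.485/0.667 = 5.23. ρ = 0.7: 3.485/0.8 = 4.36.
- Interaction: λ = 8 × (2/3)d² / (1−ρ), df 2, 60. ρ = 0.5: 5.227/0.5 = 10.45. ρ = 0.7: 5.227/0.3 = 17.42.
- Unadjusted t test at one post-test: λ = 8d² = 7.84, df 1, 30.
- ANCOVA at one post-test: λ = 8d² / (1−ρ²), df 1, 29. ρ = 0.5: 7.84/0.75 = 10.45. ρ = 0.7: 7.84/0.51 = 15.37.
- ANCOVA on the mean of both post-tests: λ = 8d² / ((1+ρ)/2 − ρ²), df 1, 29. ρ = 0.5: 7.84/0.5 = 15.68. ρ = 0.7: 7.84/0.36 = 21.78.

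| Test | 0.99 SD, ρ 0.5 | 0.99 SD, ρ 0.7 | 0.8 SD, ρ 0.5 | 0.8 SD, ρ 0.7 |
|---|---|---|---|---|
| Group main effect | 60% | 52% | 43% | 37% |
| Time-by-group interaction | 81% | 96% | 62% | 85% |
| Unadjusted t, one post-test | 77% | 77% | 59% | 59% |
| ANCOVA, one post-test | 88% | 97% | 71% | 87% |
| ANCOVA, mean of post-tests | 97% | 99% | 87% | 95% |

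**4. Sensitivity to ρ.** At ρ = 0.3 and 0.99 SD the interaction (66%) is slightly weaker than the group effect (70%), and ANCOVA on the post-test mean has 95%. In this working, ANCOVA on the mean was at least as powerful as every listed test for ρ from 0.3 to 0.8.

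**The case against.** The strongest reply is that the planned ANOVA already contains a sound test. The time-by-group interaction compares change from baseline between arms, free of the dilution, and a focus on differences between the groups can be met by it. In a 1:1 randomized trial, preferring ANCOVA is a matter of efficiency and does not correct an invalid test. Against ANCOVA at a single post-test the interaction gives up little: at 0.99 SD, 81–96% against 88–97%. All of this stands, and it limits the point in three ways.

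- A reader might infer that the whole plan ignores baseline. It does not: the interaction uses it. Only the narrower statement holds, that baseline is nowhere a covariate.
- A reader might infer that the Abstract's tests compare no arms. That is true of the paired tests only; the independent t and Mann-Whitney tests do compare them.
- A reader might infer that the diluted group effect is the trial's main test. The article designates no effect. The fault is that the choice is open, so the group effect could be used.

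The reply does not remove the conflict between the two sections. An article may leave detail to a fuller document, but this one states two different plans, and a fuller document cannot make both of them the plan. Nor does the reply cover non-normal data, where Friedman is one of the two fallbacks offered and compares no arms.

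**Conclusion.** The point holds in this limited form. The contradiction between the Abstract and the Statistical Analysis section, the undesignated treatment test, and the presence of tests that compare no arms can be read directly from the text and need no assumption. These must be settled before data collection. The (d1+d2)/3 result needs only randomization; the exact two thirds also needs an equal effect at both post-tests.

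The size of the consequence is conditional. Under the assumptions above, the between-arm tests that the article allows run from 52% to 96% power at 0.99 SD on the same 32 patients, and the group effect falls well short of the stated 80%. The large gain from baseline adjustment (97–99%) belongs to the contrast averaged over both post-tests. A baseline-adjusted contrast at one time gains about 7 points over the interaction at ρ = 0.5 and almost nothing at ρ = 0.7. The case for ANCOVA is therefore a free improvement in efficiency, separate from the reconciliation, which is necessary.

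**What to change.** State the same single analysis in the Abstract and in the Statistical Analysis section:

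- **Model:** ANCOVA, or a mixed model (available in SPSS), of the Post-test 1 and Post-test 2 values with arm, time, arm-by-time and the baseline value as covariate.
- **Test of VR:** the arm difference averaged over both post-tests, reported as an adjusted mean difference with 95% CI.
- **Non-normal data:** a method that compares arms, for example baseline-adjusted GEE or rank ANCOVA, in place of Friedman.
- **Not evidence of efficacy:** the three-visit group main effect, the time main effect, and the paired t, Wilcoxon and Friedman tests. Within-arm changes may be described.

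Cost: wording only, with the same patients, measurements and software; the Results section says the study is still in preparation. The drawback is that the main result averages over two times, so the separate contrasts immediately after the session and at 15 minutes become secondary. If the investigators prefer one time point, they should name it and accept the smaller gain shown in the table.
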